#### Exploratory purpose

Univariate and multivariate analysis of the correlation between the molecular type, immune microenvironment, gene expression profile, tumor mutation burden, ctDNA clearance, etc. of LS-SCLC patients and the efficacy of PARPi consolidation therapy;Construct a biomarker prediction model for PARPi consolidation therapy-related adverse reactions based on the molecular characteristics of small cell lung cancer patients;The correlation between the changes of DNA damage repair genes before and after concurrent chemoradiotherapy and the curative effect of concurrent chemoradiotherapy.

#### Eligibility criteria

*Inclusion criteria*

The patient or a legally authorized representative must provide study-specific informed consent prior to study entry, had good compliance, and cooperated with the follow-up.Age at least 18 years.Pathologically (histologically or cytologically) proven diagnosis of limited stage small cell lung cancer (Stage Tx, T1-T4, N0-3, M0, American Joint Committee on Cancer staging, 8th edition), within 60 days prior to registration.Patients must have measurable disease (per Response Evaluation Criteria in Solid Tumors [RECIST], version 1.1) prior to the required cycle of cCRT.Patients must be free of disease progression and not be able to receive other antitumor therapy within 6 weeks of completion of cCRT.Patients must submit archived or freshly biopsied tumor tissue (formalin-fixed, paraffin-embedded tissue block or approximately 15 unstained sections [must have > 8 sections]) along with the relevant pathology report.Eastern Cooperative Oncology Group (ECOG) performance status of 0–2 within 30 days prior to registration.Patient life expectancy must be > 12 weeks.

*Exclusion criteria*

Mixed SCLC or NSCLC confirmed by histology.Previous tumor resection for LS-SCLC.Any patient treatable by surgery or stereotactic body radiation therapy/stereotactic ablative radiation therapy should be excluded.Expected to receive any other form of anti-tumor therapy during the study period.Previous treatment with PARP inhibitor drugs.Any active malignancy within 2 years prior to enrollment, excluding the specific cancers being studied in this study and locally recurrent cancers that have been cured (e.g., resected basal or squamous cell skin cancer, superficial bladder cancer, cervical cancer carcinoma in situ or carcinoma in situ of the breast).Women who are pregnant, breastfeeding, or planning to become pregnant during the study.Concurrent participation in another therapeutic clinical trial.

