**Methods:**

This single-arm, open-label phase II trial will enroll patients aged 18–75 years with histologically/cytologically confirmed, limited-stage SCLC who have not progressed following definitive platinum-based cCRT and have an ECOG PS of 0 or 1. Patients will be excluded if they have histologically confirmed mixed SCLC or NSCLC, or have undergone previous tumor resection, or can be treated with surgery or stereotactic body radiation therapy/stereotactic ablative radiation therapy. Participants will receive pamiparib 40 mg twice daily every 3 weeks within 2 to 6 weeks after cCRT for up to 1 year or until disease progression according to RECIST v1.1. The primary endpoint is the 1-year progression-free survival (PFS) rate assessed by investigators per RECIST v1.1. Secondary endpoints include PFS, objective response rate, and duration of response assessed by investigators per RECIST 1.1, overall survival, time to distant metastasis, and safety.

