#### Chemotherapy

The chemotherapy regimen was cisplatin 25 mg/m^2^ on day 1 combined with etoposide 100 mg/m^2^ on days 1, 2 and 3 for 4 cycles. Dosage adjustments based on renal, hematologic, or other toxicity are permitted after the first cycle. If patients have contraindications or intolerance to cisplatin, carboplatin and etoposide will be used as alternative chemotherapy regimens. Carboplatin should be infused intravenously over 15 to 60 min on day 1 of each cycle at a dose of area under the plasma or serum concentration-time curve of 5 (AUC 5) every 3 weeks for 4 cycles and should be administered on Etoposide 100 mg/m^2^ was administered on days 1, 2, and 3 of each cycle for a total of 4 cycles.

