#### Radiotherapy

RT should be started after the end of the second cycle of chemotherapy. If this is not possible, RT should be started no later than the end of the third cycle of chemotherapy.

Before enrolling any patient into this study, a radiation oncologist will evaluate a chest CT scan or MRI to ensure that the treatment volume is unlikely to significantly exceed the prescribed normal tissue tolerance and that the patient is receiving RT within the dose range allowed by the protocol. feasible. Patients were excluded if their radiotherapy plan was likely to result in > 20 Gy (V20) radiation doses to greater than 38% of the whole lung volume.

All patients will be treated with standardized three-dimensional conformal radiotherapy techniques or intensity-modulated radiotherapy or volumetric rotational intensity-modulated radiotherapy on a linear accelerator with beam energy > 6 MV. The total dose of RT was 54 to 60 Gy once daily for 6 to 7 weeks.

Since SCLC is sensitive to chemotherapy and RT may not be started until cycle 2 or later (at the latest on day 1 of cycle 3), tumor shrinkage may occur from diagnosis to RT. The recommended field includes the entire affected lymph node region at the time of diagnosis, but the radiotherapy profile of the primary lung tumor can be delineated by the post-chemotherapy volume.

PCI is at the discretion of the investigator. The preferred total dose for whole-brain PCI is 25 Gy delivered in 10 divided doses, once daily.

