### Sample size calculation

This study will conduct a single-arm, phase II clinical trial in patients with LS-SCLC who have not progressed after platinum-based cCRT. Selected patients will receive consolidation therapy with pamiparib monotherapy, with 1-year PFS as the end point of the study to evaluate the efficacy and related toxicity of pamiparib consolidation therapy. In previous studies of cCRT in LS-SCLC, the 1-year PFS rate was only 43.8–52.8% [31–33]; patients received tarazopanib 1.0 mg/d, and the median PFS was 11.1 weeks [34]. We presupposed that the study protocol would increase PFS from 45 to 60%, α = 0.1, and 39 patients were expected to be enrolled, and 10% dropout was considered, and a total of 44 patients were enrolled. The final analysis of PFS was estimated to be approximately 12 months after the last patient was enrolled to ensure mature PFS data and long-term safety follow-up.

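### Diagnosis must fall within 60 days before registration, which no patient registered after the scheduled cCRT can meet; registration, enrolment and cCRT are never put in order

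*Protocol article*

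**What the plan says.** **Entry after cCRT.** The abstract's Methods describe patients with "limited-stage SCLC who have not progressed following definitive platinum-based cCRT". Study design and Sample size calculation describe the same population. The inclusion list adds: "Patients must be free of disease progression and not be able to receive other antitumor therapy within 6 weeks of completion of cCRT".

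**Entry close to diagnosis.** The same inclusion list requires a pathologically proven diagnosis and limits its timing: "American Joint Committee on Cancer staging, 8th edition), within 60 days prior to registration".

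**Entry before radiotherapy.** The Radiotherapy section says: "Before enrolling any patient into this study, a radiation oncologist will evaluate a chest CT scan or MRI". It also excludes patients whose radiotherapy plan is expected to exceed a lung V20 limit.

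**Treatment schedule.** The cisplatin regimen includes "etoposide 100 mg/m^2^ on days 1, 2 and 3 for 4 cycles", with no cycle interval given. Carboplatin is given "every 3 weeks for 4 cycles". Radiotherapy is once daily over 6 to 7 weeks. It starts after cycle 2 or, failing that, by the end of cycle 3. A later paragraph of the same section allows a start from cycle 2 and sets the latest start at day 1 of cycle 3.

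**Clock and analysis.** Study endpoints count the primary 1-year percentage from the end of cCRT. Sample size calculation puts the final analysis at a date "estimated to be approximately 12 months after the last patient was enrolled".

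**The concern.** Registration, enrolment and study entry are all used, and none is tied to cCRT. If registration follows cCRT, the 60-day rule rejects the very patients the trial is meant to treat. Sites would then have to record deviations or register earlier.

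If sites register and enrol before cCRT to satisfy the rule, two problems follow. Patients who progress during cCRT could be counted in the 44, although they never belong to the stated population and would not start pamiparib. And 12 months from enrolment is less than 12 months from the end of cCRT.

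Sites could resolve this differently. In a single-arm trial judged against a fixed 45%, who enters the denominator and how long each patient is followed bear directly on the primary result.

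**Working it through.** **Plan's own figure.** 39 / (1 − 0.10) = 43.3, rounded up to 44. This agrees with Sample size calculation. The timing check does not depend on it, but 44 is used in the last step.

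**End of cCRT.** Day 1 is the first chemotherapy dose. Cycles are 21 days (stated for carboplatin, assumed for cisplatin).

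- Day d of cycle k falls on day 21 × (k − 1) + d. The last chemotherapy day, cycle 4 day 3, is 63 + 3 = day 66.
- Radiotherapy of w weeks starting on day s ends on day s + 7w − 1.
- cCRT ends on the later of the two.

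| Radiotherapy start | Ends, 6 weeks | Ends, 7 weeks | cCRT ends |
|---|---|---|---|
| Cycle 2 day 1 (day 22) | 63 | 70 | day 66–70 |
| After cycle 2 (day 43) | 84 | 91 | day 84–91 |
| After cycle 3 (day 64) | 105 | 112 | day 105–112 |

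The table covers both of the protocol's statements of the latest radiotherapy start.

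**Against the 60-day limit.** Suppose diagnosis falls on the day of the first dose. The time elapsed at the end of cCRT is then 66 − 1 = 65 days at the least and 112 − 1 = 111 days at the most. Every schedule exceeds 60 days, by 5 to 51 days. Any gap between diagnosis and first dose, or between cCRT and the check for progression, adds to this. The floor is set by the four chemotherapy cycles, so starting radiotherapy earlier does not remove it.

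**Follow-up at the planned analysis, if enrolment is day 1 of chemotherapy.** With cCRT ending on day E, follow-up from the end of cCRT is 365 − (E − 1) days.

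- E = 66: 300 days, 65 short of a year.
- E = 112: 254 days, 111 short of a year.

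In months the shortfall is 65 / 30.4375 = 2.1 to 111 / 30.4375 = 3.6. It therefore touches patients enrolled in about the last 2–4 months of accrual.

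**How many patients.** The accrual time is not stated. Assuming uniform accrual over A months, the number is 44 × shortfall / (30.4375 × A).

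| A (months) | 65 days short | 111 days short |
|---|---|---|
| 12 | 7.8 | 13.4 |
| 24 | 3.9 | 6.7 |
| 36 | 2.6 | 4.5 |

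That is about 3–13 of 44. Any of them who had already progressed or died would have a known outcome; the rest would not.

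**Other entry points.** Enrolment at a radiotherapy start on day 43 leaves a shortfall of 84 − 43 = 41 to 91 − 43 = 48 days. Enrolment on day 60, the last day the rule could allow, with cCRT ending on day 66, leaves 6 days.

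**The case against.** The strongest reply is that the protocol uses two words for two events. The 60-day window is tied to registration, and the final analysis is tied to enrolment. If patients are registered before cCRT and enrolled into consolidation after it, the 60-day rule can be met, and 12 months from the last enrolment covers one year from the end of cCRT. The abstract's use of enrolment fits this. The flowchart was not available here and the full protocol is not shown; either may set out the order. This reply stands in part. It shows that a coherent reading exists, so a reader should not infer that either nobody is eligible or the analysis date must fail. But the article does not state that order, and the Radiotherapy section uses enrolling for a step before radiotherapy.

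Registration during cCRT is a further possibility. It can meet 60 days, but at that point the patient cannot yet be shown free of progression after cCRT.

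A reader might also infer that the 1-year endpoint would be unobserved at the analysis. That goes too far. Even with enrolment at the start of chemotherapy, only late entrants are affected, and the analysis date is approximate. PFS as a secondary endpoint censors patients without progression at their latest imaging. The primary endpoint, however, is written as a percentage of patients, with no stated treatment of an event-free patient followed for under a year.

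Nor does the protocol say that patients progressing during cCRT are counted. Its descriptions of the population point the other way. The risk arises only if entry precedes cCRT.

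Finally, the exploratory aim on "changes of DNA damage repair genes before and after concurrent chemoradiotherapy and the curative effect of concurrent chemoradiotherapy" might be taken as proof of entry before cCRT. It is not: archived tissue is accepted, so material from before cCRT could be obtained later, and response can still vary among patients without progression. No change to that aim is needed on this ground.

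**Conclusion.** The contradiction holds. A patient registered after the cCRT course as scheduled cannot have been diagnosed within the preceding 60 days. The minimum is 65 elapsed days, and the usual schedule gives 83–90. This assumes 21-day cisplatin cycles and a course given in full. The protocol also points both ways on whether entry precedes or follows radiotherapy.

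The consequences for the primary endpoint are conditional. If enrolment is at the start of chemotherapy, the last patients are 65–111 days short of one year, about 3–13 of 44 under an assumed uniform accrual of 12–36 months, and patients who progress during cCRT could be counted. If enrolment follows cCRT, neither problem arises, but then registration must be a separate, earlier event for the 60-day rule to work, and the text must say so.

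**What to change.** 1. Define registration and enrolment relative to cCRT, and use each term for one event throughout.
2. Anchor the 60-day diagnosis window to an event it can fit, for example the start of cCRT or an explicit registration step before cCRT.
3. Reconcile the Eligibility criteria with the checks the Radiotherapy section places before enrolment, including the V20 exclusion, and reconcile that section's two statements of the latest radiotherapy start. Which clinical rule applies is for the investigators; this point takes no view.
4. State that the 44 patients, and the denominator of the primary endpoint, are patients confirmed free of progression after cCRT.
5. Time the final analysis at 12 months, plus a scan window, after the last patient's end of cCRT.

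The cost is a short wording amendment with no extra patients or procedures. If enrolment has in practice preceded cCRT, the data cut moves back by about 2–4 months plus the scan window.

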### Intervention

Eligible patients will receive Pamiparib 40 mg twice daily every 3 weeks after cCRT up to 1 year or disease progression according to RECIST v1.1 occur.

#### Chemotherapy

The chemotherapy regimen was cisplatin 25 mg/m^2^ on day 1 combined with etoposide 100 mg/m^2^ on days 1, 2 and 3 for 4 cycles. Dosage adjustments based on renal, hematologic, or other toxicity are permitted after the first cycle. If patients have contraindications or intolerance to cisplatin, carboplatin and etoposide will be used as alternative chemotherapy regimens. Carboplatin should be infused intravenously over 15 to 60 min on day 1 of each cycle at a dose of area under the plasma or serum concentration-time curve of 5 (AUC 5) every 3 weeks for 4 cycles and should be administered on Etoposide 100 mg/m^2^ was administered on days 1, 2, and 3 of each cycle for a total of 4 cycles.

#### Radiotherapy

RT should be started after the end of the second cycle of chemotherapy. If this is not possible, RT should be started no later than the end of the third cycle of chemotherapy.

Before enrolling any patient into this study, a radiation oncologist will evaluate a chest CT scan or MRI to ensure that the treatment volume is unlikely to significantly exceed the prescribed normal tissue tolerance and that the patient is receiving RT within the dose range allowed by the protocol. feasible. Patients were excluded if their radiotherapy plan was likely to result in > 20 Gy (V20) radiation doses to greater than 38% of the whole lung volume.

All patients will be treated with standardized three-dimensional conformal radiotherapy techniques or intensity-modulated radiotherapy or volumetric rotational intensity-modulated radiotherapy on a linear accelerator with beam energy > 6 MV. The total dose of RT was 54 to 60 Gy once daily for 6 to 7 weeks.

Since SCLC is sensitive to chemotherapy and RT may not be started until cycle 2 or later (at the latest on day 1 of cycle 3), tumor shrinkage may occur from diagnosis to RT. The recommended field includes the entire affected lymph node region at the time of diagnosis, but the radiotherapy profile of the primary lung tumor can be delineated by the post-chemotherapy volume.

PCI is at the discretion of the investigator. The preferred total dose for whole-brain PCI is 25 Gy delivered in 10 divided doses, once daily.

#### Pamiparib

In patients who have not progressed after concurrent chemoradiotherapy, Pamiparib will start treatment within 2–6 weeks after concurrent chemoradiotherapy as determined by the investigator. The recommended clinical current routine use dose is 40 mg (2 capsules), 2 times a day, orally; Continue dosing for up to 12 months or until RECIST version 1.1-defined disease progression, unacceptable toxicity, death, or another discontinuation criterion, whichever occurs first.

### Sample size calculation

This study will conduct a single-arm, phase II clinical trial in patients with LS-SCLC who have not progressed after platinum-based cCRT. Selected patients will receive consolidation therapy with pamiparib monotherapy, with 1-year PFS as the end point of the study to evaluate the efficacy and related toxicity of pamiparib consolidation therapy. In previous studies of cCRT in LS-SCLC, the 1-year PFS rate was only 43.8–52.8% [31–33]; patients received tarazopanib 1.0 mg/d, and the median PFS was 11.1 weeks [34]. We presupposed that the study protocol would increase PFS from 45 to 60%, α = 0.1, and 39 patients were expected to be enrolled, and 10% dropout was considered, and a total of 44 patients were enrolled. The final analysis of PFS was estimated to be approximately 12 months after the last patient was enrolled to ensure mature PFS data and long-term safety follow-up.

## Discussion

PARPi as a single agent, or in combination with other antitumor regimens for SCLC, has been evaluated mainly in the extensive stage. Single-agent niraparib maintenance therapy demonstrated a moderate improvement in the PFS of platinum-responsive ES-SCLC patients [35]. In a phase II trail, the combination therapy with durvalumab and olaparib revealed an ORR of 10.5% and clinical benefits in 21% of patients in 20 recurrent SCLC patients [36]. The potential use of PARPi as maintenance therapy in SCLC has been also evaluated. A randomized phase III trial evaluating olaparib maintenance demonstrated a slight improvement of median PFS for chemotherapy-sensitive SCLC patients, although OS showed no benefit [37]. Notably, this study did not specifically select for SCLC patients, with only 30% of the experimental group representing limited-stage disease, and a mere 5–8% completing concurrent radiotherapy. Based on these evidences, we conducted a phase II trial to investigate the efficacy of pamiparib, with 16-fold higher PARP1 trapping capability compared to olaparib demonstrated in an in vivo HR-deficient xenograft model [25], in consolidation therapy for LS-SCLC. This study holds promising prospects for achieving favorable outcomes.

The Pamiparib we have chosen has three main advantages. Firstly, compared to the previous PARP inhibitor, Pamiparib has stronger drug efficacy and higher PARP1 trapping ability. Secondly, extensive preclinical investigations have demonstrated the radiosensitizing properties of PARP inhibitors. These inhibitors exhibit various effects, including the direct inhibition of repairing single-strand breaks (SSBs) caused by exposure to ionizing radiation (IR), delayed base excision repair (BER), facilitation and disruption of replication forks, ultimately leading to increased formation of DSBs following radiotherapy [38, 39]. PARPi also improve tumor hypoxia thereby enhance its sensitivity to IR [40]. Furthermore, studies indicate that PARP inhibitors can enhance radiotherapy-induced ferroptosis and trigger antitumor immune responses through the cGAS signaling pathway [41]. Thirdly, Pamiparib demonstrates exceptional penetration capabilities across the BBB. Research has confirmed its strong BBB permeability, thereby enhancing the effectiveness of TMZ in SCLC brain metastasis and glioblastoma models [25]. Preclinical studies have revealed that Pamiparib more effectively enhances radiotherapy compared to Veliparib in high-grade glioblastoma models, highlighting the combined benefits of radiosensitization and BBB penetration conferred by Pamiparib [42]. The brain is the most common site of distant failure in patients diagnosed with LS-SCLC who undergo cCRT. Historical studies have reported brain recurrence rates ranging from 20 to 29% [43–45]. Pamiparib has the potential to reduce the risk of brain metastases and offer corresponding survival benefits as a consolidation therapy following cCRT in LS-SCLC patients.

In conclusion, this is the first study to evaluate the efficacy and safety of pamiparib as consolidation treatment after concurrent chemoradiotherapy in patients with LS-SCLC. The results of our clinical trial will provide valuable information for developing new treatment strategies for these patients.

## Data Availability

The datasets used and/or analyzed in the current study are available from the corresponding author on reasonable request.

## Abbreviations

LS-SCLC: Limited-staged small cell lung cancer
PARP: Poly(ADP-ribose) polymerases
cCRT: Concurrent chemoradiotherapy
HR: Homologous recombination
ROS: Reactive oxygen species
CNS: Central nervous system
BBB: Blood-brain barrier
RECIST: Response evaluation criteria in solid tumors
PFS: Progression free survival
mOS: Median overall survival
BER: Base excision repair
SSB: Single-strand breaks
IR: Ionizing radiation
DSB: Double-strand breaks
